Therefore, the main objective of this clinical study is to evaluate the efficacy of a low-histamine diet and/or DAO supplementation over a three-month period in improving symptoms of histamine intolerance caused by DAO deficiency. Additionally, the impacts of these dietary strategies on the composition of intestinal microbiota, urinary profile of histamine metabolites, serum DAO activity, and plasma histamine levels will be assessed throughout the intervention.

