#### 2.2.3. Intestinal Microbiota Composition

To study the profile and composition of the intestinal microbiota, bacterial DNA is isolated from stool samples using the QIAamp Powerfecal pro DNA kit (Qiagen GmbH, Hilden, Germany) according to the manufacturer’s instructions, and the DNA concentrations are determined by NanoDrop 2000 (Thermo Fisher Scientific, Wilmington, DE, USA). Subsequently, the V3–V4 region of bacterial 16S rRNA is sequenced on the Illumina MiSeq platform. Bioinformatic analysis for bacterial composition will be performed using the EzBioCloud Database (ChunLab, Inc., Seoul, Republic of Korea). Differences among study groups will be analyzed using the Kruskal–Wallis test. Alpha diversity will be described using the Shannon–Weaver Index and Simpson’s Index and beta diversity using Bray–Curtis and UniFrac methods [51].

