Beyond symptom improvement, this study also examines the impact of dietary treatment on the intestinal microbiota composition in histamine-intolerant individuals. Although scientific literature on this topic is still limited, it has been hypothesized that intestinal dysbiosis could be a factor in the origin of this condition [51,52]. These previous studies coincide in describing a significant difference in bacterial diversity in those suffering from histamine intolerance, with an imbalance towards a higher presence of histamine-forming bacteria. Moreover, Sánchez-Pérez et al. (2022) identified a lower abundance of bacteria associated with gut health in patients diagnosed with histamine intolerance [51]. In another pilot study involving a small population, the same authors observed a reduction in the proportion of histamine-secreting bacteria and an increase in gut health-related species during the follow-up of a low-histamine diet [53]. By studying the intestinal microbiota composition, this study offers a foundation for future research to provide more scientific evidence about the role of gut microbiota in histamine intolerance, particularly whether intestinal dysbiosis is a cause or consequence of this food intolerance. These insights could guide subsequent investigations into the potential therapeutic role of probiotics in patients with dysbiosis-related histamine intolerance.

It is plausible to hypothesize that histamine intolerance due to DAO deficiency may lead to changes in the urinary metabolome, resulting in distinct metabolic phenotypes that can differentiate affected individuals. Indeed, in previous research, significant differences in the urinary concentration of methylhistamine were found, with markedly lower levels in individuals with histamine intolerance, compared to a control group [54]. In the current clinical trial, both targeted and untargeted metabolomic approaches in a large patient cohort will facilitate their validation as objective, reliable, and less-invasive biomarkers for histamine intolerance, providing the scientific basis for their future use as a complementary diagnostic tool alongside the current method, which primarily relies on patient anamnesis.

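### The stated microbiota test, an unadjusted eight-group Kruskal–Wallis beside diversity indices, is inefficient for the diet effect on histamine-forming bacteria that the Discussion reports

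*Protocol article*

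**What the plan says.** The Introduction lists, as an additional objective, "the impacts of these dietary strategies on the composition of intestinal microbiota". Section 2.2.3 sets out 16S V3–V4 sequencing and then three analysis steps:

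- Taxonomy: "Bioinformatic analysis for bacterial composition will be performed using the EzBioCloud Database".
- Group comparison: "Differences among study groups will be analyzed using the Kruskal–Wallis test". The variables tested are not named.
- Diversity: "Alpha diversity will be described using the Shannon–Weaver Index", together with Simpson's index; Bray–Curtis and UniFrac serve for beta diversity.

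The Discussion gives the background. Earlier studies agree in "describing a significant difference in bacterial diversity in those suffering from histamine intolerance", "with an imbalance towards a higher presence of histamine-forming bacteria". On the low-histamine diet, a small pilot "observed a reduction in the proportion of histamine-secreting bacteria and an increase in gut health-related species".

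The design in section 2.1 is two diets by four supplements, 50 per group, with 10% drop-out allowed for. Stool is collected at baseline (2.1.2), and the microbiota is assessed again after months one, two and three (2.1.4).

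**The concern.** The only diet effect on the microbiota that the article reports is directional and concerns groups of bacteria defined by function. The stated methods fit that effect poorly in three ways.

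1. Shannon and Simpson depend on the abundances, not on which taxa hold them. Bray–Curtis and UniFrac show that profiles differ, but not whether histamine-forming bacteria fell.
2. A Kruskal–Wallis test among the study groups asks whether any of eight groups differs. A diet effect is one contrast, four groups against four, and the eight-group test spreads it over seven degrees of freedom.
3. Kruskal–Wallis takes no covariate, so the baseline stool sample goes unused. For symptoms, section 2.2.1 does plan covariance analysis with baseline values.

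At stake is a modest but real fall in the relevant bacteria going undetected, or being lost among chance results from many single-taxon tests.

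**Working it through.** The article states no power, effect size or SD for the microbiota, so there is no figure to reproduce.

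**Inputs from the article.** 8 groups of 50; after 10% drop-out 50 × 0.9 = 45 per group; 4 × 45 = 180 per diet.

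**Assumed inputs.** A fall of 20%, 30% or 50% in relative abundance in the four low-histamine groups only; SD of log abundance 1.0 or 1.5; baseline-to-follow-up correlation 0.5; two-sided 5% level.

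**Step 1: are the alpha-diversity indices blind to identity?** Take one taxon at 6%, one at 3%, and 60 others sharing 91%. Let the first two swap, so one halves and the other doubles. Shannon stays at 4.0857 and Simpson at 0.9817, exactly unchanged. Bray–Curtis distance is (0.03 + 0.03)/2 = 0.03.

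**Step 2: eight-group test against diet contrast, with the target abundance as the tested variable.** For the contrast, z = −ln(1 − fall) / (SD × √(2/180)) and power ≈ Φ(z − 1.96). For a 20% fall and SD 1.0: 0.2231 / 0.1054 = 2.12, power Φ(0.16) = 56%. The eight-group test has the same noncentrality, 2.12² = 4.48, but on 7 degrees of freedom (critical value 14.07), giving 28%. Simulation with the rank tests themselves (1,500 runs per case) gave slightly lower values for the contrast and similar or slightly lower ones for the eight-group test.

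Baseline as covariate multiplies the residual variance by 1 − 0.5² = 0.75, so z is divided by √0.75 = 0.866.

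| Fall | Log SD | Eight-group Kruskal–Wallis (simulated) | Pooled diet rank test (simulated) | Diet contrast with baseline (formula) |
|---|---|---|---|---|
| 20% | 1.0 | 26% | 54% | z = 2.44, 69% |
| 20% | 1.5 | 14% | 29% | z = 1.63, 37% |
| 30% | 1.0 | 65% | 90% | z = 3.91, 97% |
| 30% | 1.5 | 28% | 60% | z = 2.61, 74% |
| 50% | 1.0 | >99% | about 100% | about 100% |
| 50% | 1.5 | 89% | 99% | >99% |

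Applying Kruskal–Wallis to change from baseline would not recover the gain at this correlation: a change has 2 × (1 − 0.5) = 1.0 times the variance of a single value.

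**Step 3: if the test is run genus by genus.** Section 2.2.3 does not say so; this is one possible reading. Assume 150 genera, 15 of them histamine-forming with about 6% of reads, log SD 1.3, 8 groups of 45, and Bonferroni over 150 genera (also an assumption). In 150 replicates per case:

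- 20% fall: the pooled diet contrast on the summed share has 81% power and the eight-group test on the sum 56%. Genus-wise testing finds at least one true genus after Bonferroni in 5% of runs. At unadjusted p < 0.05 it flags about 2.2 of the 15 true genera alongside 6.6 others (chance alone predicts 135 × 0.05 = 6.75).
- 30% fall: 100% for the sum, 27% for genus-wise testing.
- Shannon and Simpson at both falls: 4–7%, about the false-positive rate.
- 50% fall: genus-wise testing also succeeds.

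A separate run of this kind, with within-person correlation 0.5 and a 20% fall, gave 90–98% for the baseline-adjusted diet contrast on the sum, 38–79% for eight-group Kruskal–Wallis on the sum, 2–3% for genus-wise Bonferroni and 4% for Shannon.

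**Step 4: sensitivity.** The summed share gains most when the forming genera vary independently. At a 20% fall, power for the sum in a re-run was 87–99% under independence, 59–69% at correlation 0.3 between those genera, and 51–59% at 0.5.

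**The case against.** The strongest reply is that taxonomic assignment yields abundances by taxon, so histamine-forming bacteria are measured and Kruskal–Wallis can be applied to them, singly or summed. This stands. A reader might infer that nothing in section 2.2.3 counts these bacteria; the section does not support that.

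Second, the rationale is broader than histamine-forming bacteria. The Discussion also cites diversity, gut-health bacteria and dysbiosis in general. So it would be wrong to call a fall in histamine-forming bacteria the only effect predicted, or the diversity indices misplaced. This stands too, and the indices should stay.

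Third, a list of taxa and a derived variable are details that a condensed article commonly leaves to the full plan. Their absence alone is no defect. But the article does fix a test, and it is the form of that test that is inefficient.

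Fourth, the Discussion allows secondary analyses that combine groups. That partly answers the eight-group problem, but the permission is general, is not tied to the microbiota, and brings no baseline adjustment.

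Fifth, the numbers depend on assumed SDs, effect sizes and independence between genera. This is correct, and it is why only the direction and the ranges are used. Nor does the article say that a null diversity result would be read as no microbiota effect; that is a risk in reporting, not a statement in the plan.

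**Conclusion.** The concern holds in a limited form. The plan will measure the relevant taxa, but the group comparison it states is poorly matched to the directional diet effect in its own Discussion, and it leaves the factorial structure and the baseline sample unused. For a modest fall (20%), moving from the eight-group test to a pooled diet contrast roughly doubles power on the same variable (14–26% to 29–54%), and a baseline covariate raises it to about 37–69% at a correlation of 0.5. Unfocused genus-wise testing with a strict correction would do much worse. At about a 50% fall the choice hardly matters. Every effect size, SD and correlation here is assumed. Priority is low: the microbiota is an additional objective, and the full plan may already contain the targeted analysis.

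**What to change.** In section 2.2.3, add a pre-specified targeted analysis, or confirm that the full plan has one:

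- Variable: per stool sample, the summed relative abundance of histamine-forming taxa, listed from the cited earlier studies and locked before unblinding, analysed on the log or rank scale. Define the same sum for gut-health taxa.
- Comparison: low-histamine against control diet, and DAO against placebo, with the participant's baseline value as covariate.
- Keep the diversity, distance and single-taxon analyses as supporting results, since diversity is part of the rationale.

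The cost is a locked list and two derived variables from data already being sequenced; no new samples or participants are needed. The downside is that the list is a proxy, because 16S sequencing identifies taxa and not histamine-forming function. The write-up should say so.

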### 2.3. Ethical Aspects and Confidentiality

The study is being carried out in accordance with the Declaration of Helsinki of 1975 and has been approved by the Bioethics and Clinical Research Committee of the Hospital Clinic de Barcelona (HCB/2022/0437). After approval, the study protocol was registered at Clinicaltrials.gov (ISRCTN64888465). All participants are informed of the study objectives and voluntarily sign an informed consent form.

All collected data are securely stored in a cloud-based spreadsheet with password-controlled access for researchers and a constant backup system. Privacy, anonymity, and confidentiality of all participant-identifying data are strictly maintained.

## 3. Discussion

The study described here is the first prospective, unicentric, double-blind, randomized, and placebo-controlled trial designed to evaluate the efficacy of combining a low-histamine diet with DAO supplementation in alleviating symptoms of histamine intolerance. Previous intervention studies have reported positive outcomes for either the low-histamine diet or DAO supplementation, although most of them have certain limitations regarding the number of patients, follow-up period, and control group [11,12,13,14,15,16,17,18,19,20,21,22,23,24,25,26,27,28,29,30,31]. In this sense, the broad majority of these studies (18 out of 21) considered small patient cohorts (fewer than 56 participants), 61% of which did not even exceed 30 patients. Although the studies conducted by Sienbenhaar et al. (2016) and Cucca et al. (2022) included larger sample sizes (157 and 146 patients, respectively), both trials entailed a significant drawback, due to the absence of a control group in their design [20,24]. In fact, the lack of a control group (i.e., not following a low-histamine diet or receiving placebo supplementation) is a recurring limitation in many of these studies (16 out of 21). Only the work performed by Izquierdo-Casas et al. (2019) included a cohort of 100 patients diagnosed with headache and DAO deficiency, with 50% receiving porcine DAO supplementation and the other half receiving a placebo [30]. Regarding the duration of the intervention, most of the studies, with the exception of three [13,18,22], were limited to a maximum of 4 weeks. For example, Mušič et al. (2013) considered a longer dietary intervention period of up to 12 months, during which patients with DAO deficiency followed a low-histamine diet. However, only 20 patients were monitored, and there was a lack of a control group [18]. The current study aims to address all these limitations by involving a total of 400 patients, including a placebo-controlled group and an intervention period of 3 months. The study design, with distinct intervention groups following a low-histamine diet and/or receiving DAO supplementation, will allow for the assessment of the impact of each treatment separately, as well as potential synergistic effects. Additionally, this clinical trial is pioneering in its evaluation of DAO sourced from plants as a dietary supplement for managing histamine intolerance.

Beyond symptom improvement, this study also examines the impact of dietary treatment on the intestinal microbiota composition in histamine-intolerant individuals. Although scientific literature on this topic is still limited, it has been hypothesized that intestinal dysbiosis could be a factor in the origin of this condition [51,52]. These previous studies coincide in describing a significant difference in bacterial diversity in those suffering from histamine intolerance, with an imbalance towards a higher presence of histamine-forming bacteria. Moreover, Sánchez-Pérez et al. (2022) identified a lower abundance of bacteria associated with gut health in patients diagnosed with histamine intolerance [51]. In another pilot study involving a small population, the same authors observed a reduction in the proportion of histamine-secreting bacteria and an increase in gut health-related species during the follow-up of a low-histamine diet [53]. By studying the intestinal microbiota composition, this study offers a foundation for future research to provide more scientific evidence about the role of gut microbiota in histamine intolerance, particularly whether intestinal dysbiosis is a cause or consequence of this food intolerance. These insights could guide subsequent investigations into the potential therapeutic role of probiotics in patients with dysbiosis-related histamine intolerance.

It is plausible to hypothesize that histamine intolerance due to DAO deficiency may lead to changes in the urinary metabolome, resulting in distinct metabolic phenotypes that can differentiate affected individuals. Indeed, in previous research, significant differences in the urinary concentration of methylhistamine were found, with markedly lower levels in individuals with histamine intolerance, compared to a control group [54]. In the current clinical trial, both targeted and untargeted metabolomic approaches in a large patient cohort will facilitate their validation as objective, reliable, and less-invasive biomarkers for histamine intolerance, providing the scientific basis for their future use as a complementary diagnostic tool alongside the current method, which primarily relies on patient anamnesis.

This study is also designed to provide valuable insights into the prevalence of genetic polymorphisms and levels of DAO activity and plasma histamine in patients with histamine intolerance. These parameters are correlated with the presence, intensity, and evolution of symptoms throughout the dietary intervention. In general, the results of this study should help to improve dietary recommendations for histamine-intolerant patients and ultimately enhance their quality of life.

The primary limitation of this study is that, despite the expected high number of participants (n = 400), the randomization into multiple intervention groups (low-histamine diet versus control, animal- and plant-based supplementation, and two dosage levels of the latter) results in a smaller sample size per group, which could potentially reduce the statistical power of the analyses. To address this, secondary analyses combining specific intervention groups, when methodologically appropriate, can be performed to effectively increase the sample size in those comparisons. Another limitation could be that the unicentric design means findings may not be generalizable to other histamine-intolerant populations and could be subject to selection bias among patients with this food intolerance. Finally, the reliability of dietary records may be influenced by recall bias or social desirability bias.

The main strength of the study is its design as a randomized clinical trial, which allows causal inference. Standardized data collection conditions for anthropometric and blood measurements, as well as for symptom recording and dietary intake frequency using validated questionnaires, are additional strengths. Overall, the findings of this clinical trial will contribute to the development of more effective and tailored dietary interventions for histamine intolerance. Specifically, robust and reliable evidence will be generated regarding the efficacy of the low-histamine diet, the current gold-standard treatment. Furthermore, the study will clarify the role of supplementation in symptom management, including the optimal type and dosage, thereby providing evidence-based recommendations for its use in clinical practice.

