#### 2.1.1. Recruitment and Eligibility Criteria

Participants are recruited during medical visits in the Allergology, Digestive, Internal Medicine, or Dermatology units of Hospital Clínic of Barcelona, based on the following eligibility criteria: age over 18 years, symptoms associated with histamine intolerance in two or more organs or systems, reduced serum DAO activity and/or any of the DAO-encoding gene variants (rs10156191, rs1049742, rs1049793, and s2052129), not having started a low-histamine diet, and not having taken DAO supplementation. The exclusion criteria are diagnosis of food or environmental allergies, pregnancy, and prescription of antibiotics and/or probiotics within the month prior to recruitment. To assess eligibility, potential participants undergo a questionnaire about histamine intolerance symptoms (Supplementary Figure S1) and an analysis of serum DAO activity and DAO-encoding gene variants, prior to signing an informed consent form (Figure 2). Serum DAO activity is analyzed using a radioimmunoassay technique, with a cut-off value of r < 12.54 U/mL indicating DAO deficiency. Genotyping of the DAO-encoding gene variants is performed by multiplex polymerase chain reaction (PCR) on the buffy coat fraction of blood samples, obtained after the centrifugation of blood collected in an EDTA vacutainer. Both analyses are conducted at the Echevarne Laboratory (Barcelona, Spain).

Eligible participants attend a pre-intervention visit, where the study objectives and procedures are explained in detail, and informed consent for the entire study is signed. Participants also receive a biological sample collection kit (for feces and urine) and instructions for proper collection procedures.

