### 2.2. Study Outcomes

#### 2.2.1. Symptoms of Histamine Intolerance

Symptoms related to histamine intolerance, listed in Figure 1, are evaluated through specific validated questionnaires as follows: (a) gastrointestinal manifestations are assessed by the Gastrointestinal Quality of Life Index (GIQLI) and Bristol Stool Scale [38,39]; (b) headaches by the Migraine Disability Assessment Scale (MIDAS) and Headache Impact Test (HIT-6) [40,41]; (c) respiratory symptoms by the Rhinoconjunctivitis Quality of Life Questionnaire (RQLQ) and Nasosinusual Symptoms Questionnaire (SNOT-22); and (d) dermatological manifestations by SCORing Atopic Dermatitis (SCORAD), the Itch Severity Scale (ISS), Quality of Life Index for Atopic Dermatitis (QoLIAD), and Dermatology Life Quality Index (DLQI) [42,43,44,45,46]. Additionally, the general quality of life of patients is assessed using the SF-36 Health Questionnaire [47].

Data obtained from these questionnaires will be used to evaluate the effectiveness of the dietary treatment in the improvement or remission of patient symptomatology. Differences among the study groups will be determined using covariance analysis with baseline parameters as covariates. A multivariate analysis adjusted for age, sex, and clinical parameters with significant baseline differences among groups will also be applied. These differences will be expressed as means (95% confidence intervals).

All collected data regarding symptomatology will also be used to assess potential correlations with other study outcomes, such the composition of intestinal microbiota, the urinary profile of histamine metabolites, serum DAO activity, plasma histamine levels, and DAO-encoding gene variants.

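### Variant prevalence and DAO levels are to be described in a cohort that was enrolled for low DAO or a variant, so the entry rule partly sets the answer

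*Protocol article*

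**What the plan says.** Section 2.1.1 of the protocol article (Recruitment and Eligibility Criteria) requires "symptoms associated with histamine intolerance in two or more organs or systems" and, in addition, "reduced serum DAO activity and/or any of the DAO-encoding gene variants". Serum DAO is judged "with a cut-off value of r < 12.54 U/mL indicating DAO deficiency". Potential participants have "an analysis of serum DAO activity and DAO-encoding gene variants, prior to signing an informed consent form", so both results exist before eligibility is decided.

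The Discussion then says the study is designed to provide "valuable insights into the prevalence of genetic polymorphisms and levels of DAO activity and plasma histamine in patients with histamine intolerance", and that these parameters are correlated with symptoms. Section 2.2.1 likewise plans to use the symptom data to "assess potential correlations with other study outcomes", and lists serum DAO activity and DAO gene variants among them.

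The Discussion also says that the metabolomic work will facilitate "validation as objective, reliable, and less-invasive biomarkers for histamine intolerance", as a basis for later diagnostic use.

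The one mention of selection bias, in the limitations paragraph of the Discussion, is attached to the single-centre design. Nothing is said about selection on genotype or DAO activity.

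**The concern.** Two of the quantities to be described, variant carriage and DAO activity, are themselves the entry criteria. A symptomatic patient with normal DAO and no variant cannot enter. The share of carriers in the cohort, and the distribution of DAO activity, therefore partly reflect who was let in.

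The same rule makes genotype and DAO activity dependent on each other among those enrolled, whatever their relation among symptomatic patients at large. Any analysis that relates either one to symptoms inherits that dependence.

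A published prevalence could be read as the frequency of these variants in people with histamine symptoms, and so influence who is tested. Symptom correlations could be read as evidence on mechanism. Neither reading would be safe without the entry rule stated beside it.

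**Working it through.** **Inputs.** From Section 2.1.1: the entry rule, the cut-off of 12.54 U/mL, and the fact that both tests are done at screening. The article gives no carrier rate, low-DAO rate, or DAO mean or SD, so there is no stated figure to reproduce. All values of g, q0, q1, mean and SD below are assumptions, shown as ranges.

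Among symptomatic candidates, let g = carrier prevalence, q0 = P(low DAO | non-carrier) and q1 = P(low DAO | carrier).

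**Step 1. Who can enter.**

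| | Low DAO | Normal DAO |
|---|---|---|
| Carrier | enters | enters |
| Non-carrier | enters | cannot enter |

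**Step 2. Prevalence.** All carriers enter, and a fraction q0 of non-carriers. Enrolled prevalence = g / (g + (1-g)q0). This exceeds g whenever q0 < 1 and 0 < g < 1.

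- g = 0.3, q0 = 0.3: 0.3 / (0.3 + 0.7 × 0.3) = 0.3 / 0.51 = 0.588, or 28.8 points too high.
- g = 0.3, q0 = 0.9: 0.3 / (0.3 + 0.7 × 0.9) = 0.3 / 0.93 = 0.323, or 2.3 points too high.

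| True g | q0 = 0.3 | q0 = 0.5 | q0 = 0.7 | q0 = 0.9 |
|---|---|---|---|---|
| 30% | 59% | 46% | 38% | 32% |
| 50% | 77% | 67% | 59% | 53% |
| 70% | 89% | 82% | 77% | 72% |
| 90% | 97% | 95% | 93% | 91% |

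**Step 3. Genotype and DAO deficiency as yes/no.** Among those enrolled, P(low | non-carrier) = 1 and P(low | carrier) = q1. The risk difference, carrier minus non-carrier, changes from q1 - q0 to q1 - 1. With q0 = 0.3 and q1 = 0.5, a true +0.20 becomes -0.50. With 0.5 and 0.7, +0.20 becomes -0.30. With 0.9 and 0.95, +0.05 becomes -0.05. A true excess of deficiency in carriers always changes sign unless every carrier is deficient.

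**Step 4. Genotype and DAO as a continuous measure.** With normally distributed DAO of common SD, the rule leaves carriers untouched and cuts off non-carriers at the threshold. The enrolled difference is then the true difference plus SD × φ(z)/q0, where z is the standard normal quantile of q0. The added term is 1.16 SD at q0 = 0.3, 0.80 at 0.5, 0.50 at 0.7 and 0.19 at 0.9. The sign reverses only if the true deficit in carriers is smaller than that term.

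A simulation (2 million draws, SD 4, cut-off 12.54, half of candidates carriers) agrees:

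| q0 | True difference (U/mL) | Enrolled difference (U/mL) |
|---|---|---|
| 0.36 | -2.0 | +2.2 |
| 0.50 | -2.0 | +1.2 |
| 0.74 | -2.0 | -0.2 |
| 0.36 | -4.0 | +0.2 |
| 0.74 | -4.0 | -2.2 |
| 0.87 | -4.0 | -3.0 |

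Reversal occurs when low DAO is not very common in non-carriers, and attenuation when it is.

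**Step 5. The correlations actually planned.** These are genotype with symptoms and DAO with symptoms. Selection reaches them through the dependence shown in Steps 3 and 4. If a variant acts on symptoms through DAO activity, the genotype-symptom correlation is pulled in the same direction as the genotype-DAO relation. The size cannot be given, because it depends on how strongly DAO drives symptoms, which the article does not state.

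**Step 6. Urinary metabolites.** All eight groups consist of patients who met the entry criteria. Specificity is the share of unaffected people who test negative, and no unaffected comparator is described, so it cannot be estimated from this cohort.

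**The case against.** **No genotype-versus-DAO correlation is planned.** A reader might infer that the trial will report carriers as having higher DAO activity than non-carriers. Section 2.2.1 and the Discussion correlate each parameter with symptoms, not with each other, so the documents do not support that prediction. What stands is the indirect effect in Step 5.

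**Inflation presupposes a reference population.** The article speaks of patients with histamine intolerance, and the Introduction confines the main objective to intolerance caused by DAO deficiency. Symptomatic patients with normal DAO and no variant may fall outside that target. This objection stands in part: on that reading the estimate is not inflated. It is circular, because carriage helps to define who counts as a case.

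**The size depends on assumed rates.** Patients are recruited for suspected intolerance, so low DAO may be common. At q0 = 0.9 the inflation is at most about 3 points. A true deficit of 0.5 SD in carriers would keep its sign, at about -0.5 + 0.19 = -0.31 SD. It would therefore be wrong to say that the association reverses as a rule. Only the yes/no form must reverse.

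**The biomarker sentence is softer than a validation claim.** It says the work will facilitate validation, and looks ahead to future use. A reader might infer a claim to establish diagnostic accuracy in this trial; the text does not go that far. The missing comparator remains.

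**These aims are peripheral.** Prevalence and diagnostic use appear in the Discussion, not among the objectives, and the modelling of correlations may be left to an analysis plan. That limits the weight of the point. It does not resolve the conflict between the stated purpose and the stated entry rule.

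**Conclusion.** The point holds in a limited form. The entry rule undermines the stated insight into variant prevalence and DAO levels. Against all symptomatic candidates, prevalence is overstated whenever some non-carriers have normal DAO: by about 2 to 3 points at q0 = 0.9 (g from 0.3 to 0.7) and by nearly 30 points at g = q0 = 0.3. These rates are assumed, and the formula takes the low-DAO-or-variant rule as the only selection at work. If intolerance is defined by the same rule, the figure is circular.

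Within the cohort, genotype and DAO are made dependent. That can attenuate a genotype-DAO association or, when low DAO is not very common, reverse it, and so distort the planned symptom correlations by an amount that cannot be stated.

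A reader might also infer that the efficacy results are compromised. They are not: the rule acts before randomization and applies alike to all eight groups. This is a matter to put right in the descriptive and correlational claims.

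**What to change.** 1. **Preferred.** Estimate variant prevalence and DAO levels, and any genotype-DAO relation of interest, in all symptomatic patients screened under Section 2.1.1, before the DAO/variant rule is applied. No new tests are needed. The cost is keeping the screening results of patients who are not enrolled, with consent for that use. Since recruitment began in June 2022, consent may be unobtainable for some already screened; item 2 then applies.
2. **Otherwise.** Limit the prevalence statement to the enrolled cohort, report by entry route (low DAO only, variant only, both), and name the entry rule as a limitation beside the single-centre caveat.
3. **Correlations in the enrolled cohort.** Analyse DAO activity against symptoms within variant carriers, whose DAO values the rule does not truncate. Do not present a genotype-symptom analysis in DAO-deficient patients only as unbiased: if variants act through DAO activity, that restriction conditions on the mediator and can hide or distort the association.
4. **Urinary metabolites.** Reword the Discussion so that this trial is said to study markers of response, and leave diagnostic validation to a study with an unaffected comparator.

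Items 2 to 4 cost only wording and analysis specification.
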